**12.11 Appendix 11: Interview Schedule: Did Not Consent**

For individuals who read the participant information sheet but decided not to take part in the study.

- First of all, could you please tell me how you found out about the study?
  - Which NHS trust/charity/social media platform was that?
- How did you find the participant information sheet?
  - Was it clear/unclear?
  - Were you able to understand what taking part would involve?
- How did you find the contact and communication from the research team?
  - What information did they provide you with?
  - Did you feel comfortable talking with them?
  - Did they ask you whether you had any questions?
- Would you feel comfortable telling me why you decided not to take part in the study?
  - *Explore whether due to randomisation, group or online format, time commitment, having to complete questionnaires, not enough information, didn’t feel like they needed body image support, inadequate contact and communication from the research team, lack of remuneration, etc.*
- What could we have done differently to make you more likely to consider taking part?
  - *Explore whether suggested changes relate to randomisation, group or online format, time commitment, questionnaires, information provided, contact and communication from the research team, remuneration, etc.*
- Do you have anything else to add, or any questions?

**12.12 Appendix 12: Interview Schedule: Dropped Out Post-Randomisation**

For participants who dropped out of the study immediately following randomisation.

- First of all, could you please tell me how you found out about the study?
  - Which NHS trust/charity/social media platform was that?
- How did you find the participant information sheet?
  - Was it clear/unclear?
  - Were you able to understand what taking part would involve?
  - Were you able to understand that you would be randomised to one of two groups?
- How did you find the contact and communication from the research team?
  - What information did they provide you with?
  - Did you feel comfortable talking with them?
  - Did they ask you whether you had any questions?
- Would you feel comfortable telling me why you decided not to continue with the study?
  - *Explore whether due to disappointment with randomisation to specific group, the period having to wait to attend ABC, time commitment, having to complete questionnaires, not enough information, didn’t feel like they needed body image support, inadequate contact and communication from the research team, insufficient remuneration, etc.*
- What could we have done differently to make you more likely to continue with the study?
  - *Explore whether suggested changes relate to randomisation, group or online format, time commitment, questionnaires, information provided, inadequate contact and communication from the research team, remuneration, etc.*
- Do you have anything else to add, or any questions?

**12.13 Appendix 13: Interview Schedule: Control Participants Dropped Out During Study**

For participants who were randomised to the control group and dropped out before the last questionnaire.

- First of all, could you please tell me how you found out about the study?
  - Which NHS trust/charity/social media platform was that?
- How did you find the participant information sheet?
  - Was it clear/unclear?
  - Were you able to understand what taking part would involve?
  - Were you able to understand that you would be randomised to one of two groups?
- How did you find the contact and communication from the research team?
  - What information did they provide you with?
  - Did you feel comfortable talking with them?
  - Did they ask you whether you had any questions?
- Would you feel comfortable telling me why you decided not to continue until the end of the study?
  - *Explore whether due to disappointment with randomisation to control group, insufficient support from the Macmillan booklet, sought separate psychological support, having to complete multiple questionnaires, questionnaire irrelevant/upsetting, inadequate contact and communication from the research team, insufficient remuneration, etc.*
- What could we have done differently to make you more likely to continue with the study?
  - *Explore whether suggested changes relate to randomisation, materials/content provided to the control group, alternative of waitlist control, time commitment, questionnaires, information provided, contact and communication from the research team, remuneration, etc.*
- What else could we do to help encourage women to take part in a future study and to stay until the end?
- Do you have anything else to add, or any questions?

**12.14 Appendix 14: Interview Schedule: Intervention Participants Dropped Out During Study**

For participants who were randomised to the intervention group and dropped out before the last questionnaire or stopped attending the sessions.

- First of all, could you please tell me how you found out about the study?
  - Which NHS trust/charity/social media platform was that?
- How did you find the participant information sheet?
  - Was it clear/unclear?
  - Were you able to understand what taking part would involve?
  - Were you able to understand that you would be randomised to one of two groups?
- How did you find the contact and communication from the research team?
  - What information did they provide you with?
  - Did you feel comfortable talking with them?
  - Did they ask you whether you had any questions?
- Would you feel comfortable telling me why you decided not to continue until the end of the study?
  - *Explore whether due to insufficient support from ABC, time commitment of ABC, group setting or dynamics of ABC, technical issues accessing ABC, sought separate psychological support, having to complete multiple questionnaires, questionnaire irrelevant/upsetting, inadequate contact and communication from the research team, insufficient remuneration, etc.*
- What could we have done differently to make you more likely to continue with the study?
  - *Explore whether suggested changes relate to ABC (e.g., materials, format, number of sessions, between-session activities), questionnaires, information provided, contact and communication from the research team, remuneration, etc.*
- What else could we do to help encourage women to take part in a future study and to stay until the end?
- Do you have anything else to add, or any questions?

**12.15 Appendix 15: Interview Schedule: Control Participants Finished Study**

For participants who were randomised to the control group and completed the whole study (i.e., completed the last questionnaire).

- First of all, how have you found taking part in this study?
- Did you feel that the information provided about the study was clear?
  - Were you able to understand what taking part would involve?
- How did you find the contact and communication from the research team throughout the study?
  - Was each stage of the research (e.g., each questionnaire) clear?
  - Did you feel comfortable corresponding with them?
- How did you feel about the 50% chance that you would be able to attend the body image programme (i.e., being randomised)?
  - How did you feel when you were told that you would not be attending the body image programme?
  - What made you decide to continue with the study, despite not being allocated to the body image programme?
- What did you think of the Macmillan booklet that you were given?
  - Were you aware of this booklet?
  - Did you read the whole Macmillan booklet?
  - Did you find it helpful/unhelpful? Why?
- Did you access any other form of support in relation to your body image?
  - What was this?
  - Was it helpful/unhelpful? Why?
- How did you find completing the questionnaires throughout the study? *(share the questionnaire to remind them of the questions)*
  - What did you think of the format by which you completed these (either paper or online). How could this be improved?
  - How did you find the time it took to complete each questionnaire?
  - How did you find the instructions for completing the different questions in the questionnaire?
  - Did you feel that the questions that you were asked were relevant?
  - Were there other impacts of your body image concerns that were not explored or asked about in the questionnaires?
- What else could we do to help encourage women to take part in a future study and to stay until the end?
- Do you have anything else to add, or any questions?

**12.16 Appendix 16: Interview Schedule: Intervention Participants Finished Study**

For participants who were randomised to the intervention group and completed the whole study (i.e., completed the last questionnaire).

- First of all, how have you found taking part in this study?
- Did you feel that the information provided about the study was clear?
  - Were you able to understand what taking part would involve?
- How did you find the contact and communication from the research team throughout the study?
  - Was each stage of the research (e.g., each questionnaire) clear?
  - Did you feel comfortable corresponding with them?
- How did you feel about the 50% chance that you would be able to attend the body image programme (i.e., being randomised)?
  - How did you feel when you were told that you would be attending the body image programme?
  - Had you not been allocated to the programme, and instead, to the other group, do you think you would have continued with the study? Why/why not?
- How long did you have to wait until you were offered a place on the programme?
  - How did you find the period waiting to attend the programme?
  - How did you cope in the interim?
- What did you think of the ABC programme?
  - Did you find the programme helpful/unhelpful? How? Why?
  - How did you find the actual sessions, including the slides and content covered? Were they clear?
  - What did you think of the activities you were asked to complete during the sessions? Individual v group?
  - What did you think of the reading and activities you were asked to complete in-between the weekly sessions? Too much?
  - What did you think of the cognitive behaviour therapy approach that was used?
  - Were there any topics you particularly enjoyed or found helpful?
  - Were there any topics you found irrelevant or unhelpful?
  - Were there any topics that you felt we missed in the programme?
  - What did you think of the length of each session, and of the overall programme?
  - What did you think of the group size? How did you find the group dynamics?
  - How did you find the psychologist and cancer support specialist delivering the sessions?
  - How did you find the online format? Did you have any difficulty joining the sessions? Did you have any difficulty communicating with others?
  - How could we improve the programme?
  - Do you think the programme should be made available to other women who have gone through breast cancer?
- What did you think of the Macmillan booklet you were also given?
  - Were you aware of this booklet?
  - Did you read the whole Macmillan booklet?
  - Did you find it helpful/unhelpful? Why?
- Did you access any other form of support in relation to your body image?
  - What was this?
  - Was it helpful/unhelpful? Why?
- How did you find completing the questionnaires throughout the study? *(share the questionnaire to remind them of the questions)*
  - What did you think of the format by which you completed these (either paper or online). How could this be improved?
  - How did you find the time it took to complete each questionnaire?
  - How did you find the instructions for completing the different questions in the questionnaire?
  - Did you feel that the questions that you were asked were relevant?
  - Were there other impacts of your body image concerns that were not explored or asked about in the questionnaires?
- What else could we do to help encourage women to take part in a future study and to stay until the end?
- Do you have anything else to add, or any questions?

**12.17 Appendix 17: Demographic and Breast Cancer Information**

**Unique Participant Code**

Your Unique Participant Code will allow us to match your questionnaire responses over time. It will also allow us to identify your data, should you wish for it to be deleted upon choosing to stop taking part in the study.

To create your Unique Participant Code, please enter the **date (day of the month) you were born,** followed by the **first three letters of your mother's maiden name**, and finally, the **last three digits of your mobile phone number**.

For example: If you were born on the 25th of January, your mother's maiden name is Jones, and the last three numbers of your mobile phone number are 705, you would enter **25JON705**

Please enter your code in the box below:

**To help us describe the types of people participating in this study, we would like to gather some information about you. Please remember that all of your answers are anonymous.**

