We will collect a variety of different type of data exploring acceptability and feasibility. This will inform the design of a future definitive RCT and help refine intervention, recruitment, and retention procedures. Figure 1 provides an outline of participant flow in the study and Table 1 provides an outline of the different assessments and their associated timepoints.

- - 1. **Quantitative measures of feasibility and acceptability**

We will collect the following quantitative data to assess feasibility and acceptability of the research design and ABC:

- - - 1. **Monitoring data**
- Rates of recruitment (and associated response rates), with attention to the method by which women were recruited and their demographic diversity.
- Rates of retention following randomisation:
  - Proportion completing ABC (number of sessions attended and between-session activities completed)
  - Proportion of control arm reading the Macmillan body image booklet (plus percentage of booklet read)
  - Proportion completing outcome measures at each assessment (plus data completeness rates; outcome measures described in 5.6.3).
    - 1. **Self-report rating scales included in outcome assessments (see 5.6.3)**
- Rating scales to explore acceptability of ABC (e.g., the group format, online nature, between-session activities; Appendix 9) - to be completed by ABC participants in the immediate post-intervention assessment, i.e., Week 9.
- A single rating scale examining how helpful participants found the ABC programme will also be included in the three- and six-month follow up assessments (see Appendix 31). This will allow monitoring of how participants’ perceptions of the programme and its impacts may develop over time.
- Rating scales to explore acceptability of the research process generally (e.g., information provided about the study, randomisation process, questionnaires; Appendix 10) – to be completed by all participants in the six-month post-intervention assessment i.e., Week 32.
  - 1. **Qualitative measures of feasibility and acceptability**

In addition to the above, we will collect the following qualitative data to assess feasibility and acceptability of the research design and ABC:

- - - 1. **Open-ended questions included in outcome assessments (see 5.6.3)**

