## **Data collection**

All data will be handled and stored securely and in compliance with the Data Protection Act and GDPR.

Personal information relating to contact details will be collected when participants provide informed consent to participate in the full study. Participants will be identified by a unique participant ID, and files linking participant ID to their contact details will be held on the University of the West of England OneDrive for Business, which is compliant with GDPR, ISO27001 and Cyber Essentials.

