| Q2. How will you collect, create or access the data? [See Note 2](https://www.uwe.ac.uk/study/library/research-support/manage-your-research-data/planning-your-project/create-a-data-management-plan#note2) |
| Data will not be collected until NHS IRAS, HRA, and UWE REC approvals have been received. All data will be handled and stored securely and in compliance with the Data Protection Act and GDPR.  Informed consent will be received from participants prior to any research data being collected. Participants will be fully informed about the study prior to providing consent, through reading of the participant information sheet and discussions with the research team. They will be given the option of completing this online via the survey software Qualtrics or via a paper version of the form. If they prefer the first option, they will be sent a weblink to the online consent form. Once completed, they will be emailed a signed copy for their records. If they prefer the second option, they will be mailed the consent form and a pre-addressed, stamped envelope to return the signed consent form via the post. Some of these participants will be purposefully sampled to take part in an interview to provide feedback about the research process or the body image programme. They will be required to read a separate participant information sheet and complete a separate consent form. The similar process as above will take place. The signed consent form will be held on UWE’s OneDrive for Business and only accessed by the research team at UWE (and paper versions will be scanned into an online file, and subsequently securely destroyed).  Participants will complete several self-report quantitative and qualitative measures at different assessment time points throughout the study exploring their feedback on the whole research process (i.e., exploring feasibility of the study) and the body image programme being evaluated. They will also be asked to provide their own demographic and cancer related information and completed validated self-report measures relating to body image, intimacy, and quality of life.  This data will be collected online via Qualtrics (whereby participants are sent the appropriate weblink), an online survey platform. Qualtrics uses Transport Layer Security (TLS) encryption (also known as HTTPS) for all transmitted data. This data will be downloaded into SPSS (a statistical software package) and NVivo (a qualitative data analysis software package) with files held on OneDrive for Business.  If participants to complete these measures by paper, they will be sent these in the post with a stamped pre-addressed envelope to return to the research team. Once returned, these will be stored in a locked filing cabinet in a locked office at the UWE Bristol, to which only the research team will have access. Once the data is inputted directly into SPSS and NVivo files on OneDrive for Business, the paper versions will be securely destroyed.  Participants will be identified by a unique participant ID (devised based on a combination of non-identifying but memorable data e.g., the number of siblings they have, the last three digits of their phone number) for the above data collection, and files linking participant ID to their contact details will be held on the UWE Bristol OneDrive for Business, with only the UWE research team (including the Statistician) having access to this. Anonymous raw data relating to the self-report quantitative and qualitative measures (including the validated self-report measures relating to body image, intimacy, and quality of life) will only be shared beyond UWE with Kings College London, so that the Health Economist can conduct their analyses. The data will be stored on their secure University OneDrive for Business. A collaboration contract has been signed between UWE and Kings College London, with includes expectations on how data will be processed and held.  Anonymised data related to the programme attendance and engagement, as well as Microsoft Teams recordings of the sessions, will be collected by programme facilitators, and shared with the research team, which will then be copied over onto UWE Bristol OneDrive for Business. No participants will be identifiable via these recordings, and only the UWE research team will access to these.  Participants taking part in the Microsoft Teams audio-recorded interviews will be given a pseudonym, and thus minimises the chances of being identifiable. The recordings via Teams will be saved into a file on the West of England OneDrive for Business, and once transcribed, they will be deleted. Only the UWE research team will have access to this data.  Other quantitative data collected throughout the trial (e.g., withdrawal rates) will be collected by the research team and saved on a file on the University of the West of England OneDrive for Business. Only the UWE research team will have access to this data. |

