| Q6. How will your data be processed? [See Note 6](https://www.uwe.ac.uk/study/library/research-support/manage-your-research-data/planning-your-project/create-a-data-management-plan#note6) |
| All personal data (i.e. names and contact details) will be stored separately from the anonymised research data (i.e. self-report measures). The personal data and participant ID will be linked in the same document, but this will only be accessible by the CI ([name]) and Research Fellow/Study Manager on the study. Personal data will only be accessed by these two individuals to enable them to contact participants at each respective assessment timepoint (i.e., to share the weblink or paper-based questionnaire with them) and to share the findings of the study (if participants indicated they would like to receive information about these).  Once this personal data is no longer needed (i.e. at the end of the research, or once the participant has been informed of the results of the study if they have requested this), it will be deleted. All research data will be anonymised (i.e., it will include no personal identifying information) and uploaded (along with the ‘coding book’ and ‘Datafile log’) to UWE Bristol OneDrive for Business. This will be shared with the Statistician based at UWE via UWE Bristol OneDrive for Business) and the Health Economist at Kings College London, who will store these files on their university’s OneDrive for Business. A collaboration contract has been signed between UWE Bristol and collaborating universities, with includes formal agreement how data will be processed and held.  No one else will have access to the quantitative data. |
| Q7. Does the Data Protection Act (2018) apply to your research? [See Note 7](https://www.uwe.ac.uk/study/library/research-support/manage-your-research-data/planning-your-project/create-a-data-management-plan#note7) |

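### Questionnaires are matched over time by a code each woman makes up herself; with no study-issued ID stated on links or paper forms, follow-up forms can avoidably lose their baseline pair.

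*Protocol*

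**What the plan says.** The baseline form in Appendix 17 asks the participant to build a code from the day of the month she was born, the first three letters of her mother's maiden name and the last three digits of her mobile number. It gives a worked example ("If you were born on the 25th of January, your mother's maiden name is Jones"), and states the purpose: "Your Unique Participant Code will allow us to match your questionnaire responses over time". A second stated use is to locate a woman's data if she leaves and asks for deletion. The same form tells women that their answers are anonymous.

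The data management plan (Appendix 29, Q2) says the participant ID is devised from memorable data. Its example is "the number of siblings they have, the last three digits of their phone number". Only the phone digits are common to the two descriptions.

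Section 8.1 is neutral on how the ID arises: "Participants will be identified by a unique participant ID, and files linking participant ID to their contact details" are kept on the university's OneDrive. Appendix 29, Q6 says the Chief Investigator and Study Manager use the linked personal data "to enable them to contact participants at each respective assessment timepoint".

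Online participants are sent a weblink and others a paper form with a return envelope (sections 5.6.3 and 8.1). The protocol does not say whether either carries an identifier, or what happens to a form whose code does not match.

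Retention and data completion are primary outcomes (Trial Summary). Section 5.6.1.1 monitors "Proportion completing outcome measures at each assessment". Section 7.2 plans ANCOVA at T2, T3 and T4 adjusted for the baseline score, and section 3 plans to use the pre-post correlation to refine the size of the definitive trial.

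**The concern.** A self-made key works only if the woman produces the same string each time over 32 weeks. The Appendix 17 recipe has weak points:

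- It does not say whether a single-digit day of birth is padded with a zero.
- It gives no instruction for a woman without a mobile phone, or whose number changes between assessments.
- Maiden-name spelling and typing slips are always possible.

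The data management plan makes the self-made code the participant ID. A mistyped code therefore does not point directly to anyone in the link file, and someone has to infer whose form it is.

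The analyses at stake need T1 joined to a later form: the baseline-adjusted comparisons, the pre-post correlation, and any statement of how many women completed all timepoints. An error in the T1 code breaks the pair at T2, T3 and T4 together. The same code is also the stated means of finding a woman's data if she asks for deletion.

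**Working it through.** The protocol gives no linkage error rate and no figure that depends on one. Its only sample-size figure, the 11% in section 3, does not enter here. The check therefore has two parts.

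**1. What the texts fix**

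| Question | Appendix 17 | Appendix 29 | Section 8.1 |
|---|---|---|---|
| Who makes the ID? | The participant | Devised from memorable data | Not stated |
| Recipe | Day of birth, maiden name, mobile digits | For example siblings, phone digits | None |
| Stated use | Match forms; find data for deletion | Identify the participant; linked to contact details | Linked to contact details |
| Study-issued ID on link or form? | Not stated | Not stated | Not stated |

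Re-entry of the code at T2-T4 is an inference, since only the baseline form shows the code box. It is a reasonable one: a code typed once could not match later forms unless they carried it too.

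**2. Size under an assumed error rate**

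Inputs:
- N = 120 (section 3).
- p = probability that a form carries a wrong code. Assumption: 1%, 3% or 5%, independent between forms and never repaired.
- True retention of 80%, for illustration. Section 1.2 reports 80% completing all timepoints in the earlier in-person study.

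Formulas:
- T1-T2 pairs lost = 1 − (1 − p)².
- Women returning all four forms but not fully linked = 1 − (1 − p)⁴.
- Pairs lost among 120 × 0.80 = 96 returned T2 forms = 96 × [1 − (1 − p)²].
- Apparent completion of all four = 0.80 × (1 − p)⁴, if counted only through matched codes.

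| p | T1-T2 pairs lost | Of 96 pairs | Not linked on all four | Apparent all-four completion (true 80%) |
|---|---|---|---|---|
| 1% | 1 − 0.9801 = 2.0% | 1.9 | 3.9% | 76.8% |
| 3% | 1 − 0.9409 = 5.9% | 5.7 | 11.5% | 70.8% |
| 5% | 1 − 0.9025 = 9.8% | 9.4 | 18.5% | 65.2% |

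Losing 2% to 10% of pairs at random would widen an ANCOVA confidence interval by about 1/√0.9801 − 1 = 1% to 1/√0.9025 − 1 = 5%.

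**Comparison with sampling error.** The 95% half-width for 80% of 120 is 1.96 × √(0.8 × 0.2/120) = 7.2 percentage points. If single-wave retention were counted through matched pairs, the shortfall would be 0.80 × 2.0% = 1.6 points at p = 1%, 0.80 × 5.9% = 4.7 points at 3%, and 0.80 × 9.8% = 7.8 points at 5%. Only the last exceeds 7.2.

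**Padding.** With birth dates spread evenly, days 1 to 9 cover about 9/30.4 = 30% of women. These are the women who could type their day in two ways. Routine cleaning would catch most such cases.

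**The case against.** The strongest case against is that the study team knows its participants. A file ties each ID to a named woman, and the Chief Investigator and Study Manager contact her at each assessment. Randomisation follows completion of baseline (section 5.4), and the voucher follows completion of T4 (section 5.7). Staff must therefore know in practice who has returned what. A stray code can be compared with the listed IDs and the outstanding forms. The weblink might be personal; the text neither says so nor rules it out. Details of this kind often sit in operating procedures.

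Much of this stands, and it rules out several stronger readings:

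- A reader might infer that mistyped codes bias retention, a primary outcome, downwards. No text counts an unmatched form as non-completion, and completion at each assessment can be counted from returned forms without any matching. The exposure is to paired analyses and to completion across all timepoints.
- A reader might infer that the two recipes cause miscoding. The data management plan's version is only an example, and participants see one explicit recipe. The difference is one of documentation.
- A reader might infer that the loss at 3% to 5% error is as large as sampling error. That fails at 3% (4.7 against 7.2 points), and it presumes the counting rule that the protocol does not state.

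What the objection does not remove is that the only stated matching key is self-made. Repair is possible but is not a stated procedure. The documents also disagree on who may open the link file: section 8.2 and Appendix 29, Q6 limit it to the Chief Investigator and Study Manager, while Appendix 29, Q2 includes the wider university team and the statistician.

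**Conclusion.** The point holds as an avoidable linkage risk, not as a demonstrated bias in retention. The protocol names a participant-made code as the key, describes it in two ways, and states no issued identifier on the forms.

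The size is unknown. Under assumed, independent and unrepaired errors of 1% to 5% per form, about 2% to 10% of T1-T2 pairs would be lost, and about 4% to 19% of women who returned all four forms would not be fully linked. These are upper figures for each error rate, because hand repair would reduce them. The cost to the ANCOVA would be modest. The stronger reasons to act are that completion across all timepoints could look worse than it is, that locating data for deletion depends on the same code, and that prevention is simple.

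**What to change.** - Issue each woman a study number at consent. Embed it in her individual Qualtrics link, pre-print it on paper forms, and use it as the matching key at T1-T4.
- Keep the self-made code at most as a cross-check.
- Count retention from returned forms logged by study number, and report any unmatched forms separately from non-return.
- Use one ID definition in Appendix 17, section 8.1 and the data management plan, and reconcile the statements on who may open the link file.

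The cost is a little survey set-up and an amendment. The participant wording must change from anonymous to coded or confidential. That is already the true position, because a link file is held.
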